#### Statistical analyses

We will test for significant differences between groups at baseline using independent samples t-tests, with α = .20 to reduce type-II error probability. For all study hypotheses tests, type-I error probability is set to α = .05. VAS and QOL data will be analyzed with ANCOVA models, where posttest values serve as criteria, pretest scores as covariates and group assignment as a fixed predictor, respectively. We will run repeated-measures ANOVA on physiological data (HRV/BVP) to test for polynomial trends over time, main effects of group allocation, and interaction effects.

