Hence, the general aim of the present study is to improve the body of research on this important but underrepresented topic. More precisely, the study goals are to evaluate the effectiveness of a music therapy relaxation intervention regarding palliative care patients’subjective perception of relaxation, well-being, and pain (i.e. immediate effects on psychological outcomes; primary outcome of this study),autonomous relaxation response indexed by HRV and BVP (i.e. immediate effects on physiological outcomes),health-related quality of life (i.e. medium-term effects).

Therefore, we compare the effects of music therapy to the ones of a control group, using a prerecorded mindfulness exercise without musical elements or therapeutic interaction. We hypothesize improvements over time in both groups, but a superiority of the music therapy intervention on all three aforementioned dimensions.

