### Study design and procedures

The study is designed as a prospective RCT with two parallel arms. Hospitalized patients eligible for study inclusion are contacted at bedside in their rooms and informed about the procedures and objectives of the study. The investigator presents the purpose of the study as to compare the effects and feasibility of two commonly used relaxation interventions for the palliative care context. No information is given about which of the two interventions is the actual experimental condition. If patients agree to participate, the investigator asks them to sign the informed consent sheet, and baseline assessment of the patients’ QOL and previous experience with relaxation techniques is obtained. Following that, the investigator gathers relevant information from the patients’ medical record and opens a serially numbered opaque envelope containing assignment to one of the two study arms (see interventions). We used a computer-based block permutation for the generation of the randomization sequence before the onset of the study. The investigator then returns to the patients’ room with the physiological measuring devices, collects pretest data on relaxation, well-being, and pain using VAS, and starts a 5-minute pretest recording of HRV. Then, either the experimental condition (music therapy) or the control condition (verbal relaxation) is initiated, lasting for twenty minutes. HRV is recorded throughout this procedure. Data collection is complemented by another five minutes of HRV recording and posttest VAS assessment following the intervention. The entire procedure lasts thirty minutes and is repeated two days later, finishing with the follow-up assessment of patients’ QOL. In both groups, the patient rests in a supine position for the entire duration of the session. Figure 1 shows a flow diagram of the study design and procedures.

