**Intervention procedures and time course.**

### Outcomes

#### VAS (primary outcome)

Patients’ subjective experience of immediate short-time effects of the intervention is measured via three different VAS, assessing relaxation *(-5 = “very tense”* to *+5 = “very relaxed”)*, general well-being *(−5 = very bad* to *+5 = very good)*, and pain intensity *(0 = no pain at all* to *10 = worst pain possible)*. The scales’ endpoints depict good vs. bad smileys and a color code from red to green for better visualization of the valences. Subjective ratings are assessed immediately before and after each session.

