### Data analysis

#### Sample size calculation

Statistical power calculations for this study are adjusted for immediate short-time effects on self-report VAS data (i.e. the primary outcome). Bradt and Dileo’s [8] findings suggest that medium sized effects are most likely to be expected for the impact of music therapy on psychosocial outcomes in palliative care. Recent articles [29, 30] on sample size calculations emphasize the superiority of ANCOVA models for analyzing the results of randomized, controlled trials over the repeated-measures ANOVA approach. The inclusion of pretest values as a covariate in these models increases statistical power (i.e., the likelihood to identify statistically significant effects).

Assuming statistical power of (1-β) = .80, type-I error probability of α = .05, and a correlation between covariate and outcome of ρ = .6, a total sample size of *N* = 84 is required to detect medium sized effects between groups [29]. With an expected drop-out rate of 10%, approximately 92 participants need to be recruited for this study. The risk of attrition bias will be addressed in the course of intention-to-treat analyses.

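### Three unranked primary VAS scales, each tested at α = .05 with no success rule, leave 5% type-I error and 80% power not jointly assured

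*Protocol article*

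**What the plan says.** The study goals in the Background section group perceived relaxation, well-being and pain under one heading: "immediate effects on psychological outcomes; primary outcome of this study". The Outcomes section, under VAS, states that the patient's experience "is measured via three different VAS, assessing relaxation", general well-being and pain intensity. No scale is ranked above another. On timing it says: "Subjective ratings are assessed immediately before and after each session". There are two sessions: "The entire procedure lasts thirty minutes and is repeated two days later".

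The Sample size calculation section ties the trial's size to this outcome: "Statistical power calculations for this study are adjusted for immediate short-time effects on self-report VAS data". It assumes 80% power, "type-I error probability of α = .05, and a correlation between covariate and outcome of ρ = .6" and a medium effect, and arrives at N = 84.

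The Statistical analyses section specifies ANCOVA of posttest on pretest and group for the VAS data, and sets one error level throughout: "For all study hypotheses tests, type-I error probability is set to" α = .05.

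The article gives no lead scale, no composite, no any-scale or all-scales criterion, and no statement of how the two sessions enter the primary comparison.

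**The concern.** The sample size belongs to a single ANCOVA contrast, but the primary outcome as defined produces at least three, each at the full .05. Nothing says what pattern of results makes the trial positive. A report could then present one significant scale out of three as a positive primary result, with a false-positive risk above the 5% the reader is told to expect. If the intention is instead that all three scales must succeed, or that α is split among them, 84 patients give less than the stated 80% power. The choice of rule therefore decides which of the two planning figures is lost, and the article leaves that choice open until results are known.

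**Working it through.** **Inputs from the article.** α = .05, power .80, ρ = .6 between pretest and posttest, medium effect, N = 84, three VAS scales, two sessions, ANCOVA.

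**Assumptions.** d = .5 for a medium effect, two-sided testing, 1:1 allocation (42 per arm). The article states none of these, but together they reproduce its N. It gives no correlations between scales or sessions, so I show ranges. All three scales are given the same d and ρ.

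**Step 1: reproduce N = 84.**
- Adjusting for the pretest multiplies the variance by 1 − .6² = .64, so the residual SD is .8.
- Normal approximation: n per arm = 2 × [.8 × (1.960 + .842)/.5]² = 40.2, rounded up to 41, so N = 82.
- From the t-test: 64 per arm × .64 = 40.96, rounded up to 41, plus 1 = 42 per arm, so N = 84 exactly.
- Power at N = 84: noncentrality = (.5/.8) × √(84/4) = 2.864 with 81 degrees of freedom, giving 80.8%.
- Alternatives do not fit: one-sided testing gives N = 64, and omitting the covariate gives N = 126.

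The article's figure is therefore correct for one two-sided test.

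**Step 2: three tests at .05, any significant scale counts.** For independent scales the false-positive rate is 1 − .95³ = .143. For correlated scales I simulated equicorrelated normal test statistics. Power to win on at least one scale comes from the same simulation with each statistic shifted by 2.864.

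| Scale correlation | False-positive rate, any scale | Power, at least one scale | Power, all three scales |
|---|---|---|---|
| 0 | 14.3% | 99% | 55% |
| .5 | 12.5% | 96% | 64% |
| .7 | 10.9% | 93% | 68% |
| .9 | 8.4% | 88% | 74% |

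**Step 3: all three scales must be significant at .05.** Type-I error is at most 5%. Power is the last column above: about 55% to 74%.

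**Step 4: Bonferroni over three scales.** At α = .05/3 = .0167, noncentral-t power at N = 84 is 66%. Reaching 80% needs N of about 112, or 112/.9 = 124.4, that is 125 recruited at the article's 10% drop-out rate.

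**Step 5, conditional: sessions tested separately.** If each scale were also tested at each session there would be 3 × 2 = 6 tests. With all six independent the any-success rate is 1 − .95⁶ = .265. With a session correlation of .5 and scale correlations from .9 down to 0, simulation gives about 15% to 25%. The article does not say that sessions are tested separately, so these figures do not belong in the main result.

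**The case against.** The strongest reply has four parts.

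1. **Multiplicity procedures are often left to an analysis plan, which is not shown here.** That is fair for the details. But this point does not rest on silence: the article itself states .05 for every hypothesis test and itself lists three primary scales. An analysis plan could repair this only by departing from the published rule.

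2. **A reader might infer that both the 5% and the 80% fail.** The documents do not support that, because no single success rule breaks both. Under an any-scale rule the error rate rises, but so does power (88% to 99% if every scale has a medium effect). Under an all-scales rule or Bonferroni, 5% holds and only power falls. What stands is that the two figures do not hold together.

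3. **A reader might also infer six primary tests.** The article says when ratings are taken, not that each session is tested on its own. The sessions could be averaged or modelled jointly. Three tests is the plain reading, and the point holds at three.

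4. **Independence is implausible for scales rated by the same patient within minutes.** Agreed, so 14.3% is an upper bound over non-negative correlations. At a correlation of .9 the rate is still 8.4%. These rates count false positives in either direction. Those favouring music therapy are about half as frequent (5.4% at .7, 4.2% at .9), to be set against 2.5% for one two-sided test, so the relative inflation is similar.

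The Background section's hypothesis of superiority on all three dimensions does not supply the missing rule. Those dimensions are psychological, physiological and quality of life, and the three VAS scales all sit inside the first.

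**Conclusion.** The point holds in this form: with three co-listed primary scales, .05 for every test and a sample sized for one test, 5% type-I error and 80% power are not jointly assured for the primary outcome. Following the article as written and counting any significant scale gives a false-positive rate of about 8% to 14%. The rules that protect the 5% leave power at about 55% to 74% (all scales) or 66% (Bonferroni). The sizes depend on the assumed d, sidedness, allocation and scale correlations. The direction does not change anywhere in the correlation range shown. N = 84 is not itself an error: it is right for a single contrast, which is why the repair is easy.

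**What to change.** Before any outcome data are seen, name one VAS scale and one between-group contrast as the sole primary test at two-sided α = .05. Relaxation is a natural choice for a relaxation intervention, but the sponsor may choose another. The contrast can be the posttest comparison at one stated session or a prespecified average over both. Move the other two scales to secondary status and test them in a stated fixed sequence after the primary test, or with Holm. N = 84 then matches its stated α and power, provided the chosen contrast meets the assumed d and ρ.

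The cost is a paragraph in the plan and a registry update, with no extra patients, and two scales lose primary status. If the sponsor wishes to keep all three as primary, the success rule must be written down with a matching α and the trial re-sized. Under Bonferroni that means about N = 112 instead of 84.

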#### HRV/BVP

During the 30-minutes intervention we collect continuous data on the intervals between successive heartbeats in milliseconds (i.e. HRV). For reason of feasibility and lower patient burden, we decided to use a BVP finger sensor with a sampling rate of 128 SPS for the least invasive signal processing, instead of a high-resolution ECG signal that would require electrode placement. A NeXus-16® interface sends the BVP signal to the BioTrace + ® software on a laptop computer via Bluetooth. BioTrace® records raw data of all sessions and exports IBI text files for each participant and session. Kubios v2.1® transforms these tables into HRV parameters based on six successive 5-minutes-samples for further statistical analyses with IBM SPSS Statistics 20®.

Despite the derivation of HRV parameters, BVP signals offer the possibility to measure vasodilation/vasoconstriction as a second set of markers on autonomous functioning. A shift to parasympathetic dominance is expected to manifest in an increase in the BVP amplitude. In accordance to the HRV analysis, we will calculate mean values and standard deviations for 5-minutes-intervals for each patient and subject.

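### For HRV/BVP, the planned six-window group main effect includes the pre-treatment window and is not adjusted for it; a baseline-adjusted contrast should replace it, and the deciding test should be named

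*Protocol article*

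**What the plan says.** The Statistical analyses section assigns ANCOVA with the pretest score as covariate to VAS and quality of life. It then turns to the physiological outcomes: "We will run repeated-measures ANOVA on physiological data (HRV/BVP) to test for polynomial trends over time, main effects of group allocation, and interaction effects". No baseline covariate is named for them and no reason is given for the change of model.

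The Sample size calculation section says that recent articles "emphasize the superiority of ANCOVA models for analyzing the results of randomized, controlled trials over the repeated-measures ANOVA approach", and adds that putting the pretest value in the model raises power.

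The HRV/BVP section says that the HRV parameters are "based on six successive 5-minutes-samples". Study design and procedures, and Verbal relaxation, give the timeline of a session: 5 minutes of recording before the intervention, 20 minutes of intervention and 5 minutes afterwards.

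The Background hypothesizes improvement over time in both arms, with music therapy superior on all three dimensions, including the autonomic response. The VAS ratings are the primary outcome; HRV/BVP is not.

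**The concern.** Six windows of 5 minutes fill the 30-minute session, so window 1 is the pre-treatment recording, windows 2–5 are the intervention and window 6 is the post recording. A group main effect in a repeated-measures ANOVA compares the arms on the average of all six. That average contains a window in which the session's intervention cannot yet have acted, and nothing removes chance differences between the arms at that window.

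The article lists main effect, interaction and trends side by side and does not say which of them decides superiority on HRV/BVP. These tests answer different questions and can disagree. A null main effect could be reported as absence of a differential autonomic response when that term was the diluted one, although the data for a sharper comparison had been collected.

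**Working it through.** **The plan's own figure.** The inputs, from Statistical analyses and Sample size calculation, are "For all study hypotheses tests, type-I error probability is set to α = .05", "Assuming statistical power of (1-β) = .80", "a correlation between covariate and outcome of ρ = .6" and a medium effect. The article gives no number for medium; d = 0.5 is assumed, two-sided, 1:1. An unadjusted t-test needs 64 per arm. Then 64 × (1 − .6²) = 40.96, rounded up to 41, plus 1 gives 42 per arm, N = 84. ANCOVA power at N = 84 is 80.8%. The stated N reproduces, and the gain from the pretest covariate is built into it. It applies to VAS; no power is stated for HRV/BVP.

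**Which windows.** 5 + 20 + 5 = 30 minutes = 6 × 5 minutes. The inclusion of window 1 in the ANOVA is inferred from these sections. The Statistical analyses section does not state it, and no section excludes it.

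**Assumptions for HRV/BVP.** n = 42 per arm, unit SD, compound symmetry with correlation ρ, one session, effect δ = 0.5 in each of windows 2–6. The value ρ = .6 is borrowed from the VAS calculation, and .4 to .8 is the range. Power is from noncentral t or F, two-sided 5%. The standard error of a group difference is √(2 × variance / 42).

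*Group main effect (mean of windows 1–6).* Difference = (5/6) × 0.5 = 0.417. Variance = (1 + 5ρ)/6 = .667. Standard error = .178, noncentrality = 2.34, power 64% (65% by the normal approximation). For any effect shape this term is 5/6 of the mean effect over windows 2–6. A chance baseline difference b adds an expected b(1 + 5ρ)/6 = .667b to the estimate.

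*Omnibus group × time.* λ = (n/2) × Σ(δₖ − mean δ)² / (1 − ρ) = 21 × .2083 / .4 = 10.94 on (5, 410) degrees of freedom, power 72%.

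*Mean of windows 2–6 adjusted for window 1.* Difference = 0.5. Residual variance = (1 + 4ρ)/5 − ρ² = .68 − .36 = .32. Standard error = .123, noncentrality = 4.05, power 98%. Information relative to the main effect: (.5²/.32) / (.417²/.667) = 3.0.

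| ρ | Main effect | Omnibus group × time | Adjusted mean, windows 2–6 |
|---|---|---|---|
| .4 | 76% | 51% | 97% |
| .6 | 64% | 72% | 98% |
| .8 | 54% | 97% | over 99% |

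**Other effect shapes, ρ = .6.**

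- Effect rising linearly from 0 in window 1 to 0.5 in window 6. Main effect: difference .25, half the final effect, power 28%. Adjusted mean of windows 2–6: difference .3, power 67%. Linear trend × group (weights −5, −3, −1, 1, 3, 5): difference 3.5, variance 70 × .4 = 28, power 85%.
- Effect in window 6 only. Main effect: difference .083, power 7.5%. Omnibus interaction: λ again 10.94, power 72%. Adjusted mean of windows 2–6: difference .1, power 13%. ANCOVA on window 6 alone: variance 1 − .36 = .64, power 81%.

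The adjusted mean beats the main effect in every scenario. It does not beat every planned test in every scenario.

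**The case against.** The strongest reply is that the same sentence also plans interaction and trend tests. Group × time compares change between arms, uses window 1 as each patient's own reference, and is the planned term closest to the stated hypothesis. That stands. A reader might infer that the whole autonomic goal rests on a diluted, unadjusted test, but the article does not support this: the defect belongs to the main-effect term alone. The simple within-patient contrast of windows 2–6 against window 1 has variance .68 + 1 − 1.2 = .48 and about 90% power (91% by the normal approximation), not far below 98%.

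A reader might also infer that the article rejects repeated-measures ANOVA and then contradicts itself. The remark on ANCOVA stands in a sample-size section tied to the VAS outcome and concerns single pre/post pairs. HRV/BVP is a six-point series within a session, and a different model for it is defensible. What remains is that a baseline was collected and the named main effect does not use it.

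A third tempting reading sets 7.5% against 81% for an effect confined to the post window. That comparison omits the planned interaction at 72%, and the 81% belongs to a window-6 analysis, not to the mean of windows 2–6, which has 13%. Nor should the trend tests become merely descriptive. The Music therapy section describes a build-up to a peak after 10 minutes and then a gradual reduction, so an immediate constant effect cannot be taken for granted, and under a gradual rise the trend test is the stronger one.

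Sphericity corrections, transformations and the handling of missing windows are details that a condensed article may leave to the full plan. They form no part of this point.

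**Conclusion.** The point holds for the group main effect on HRV/BVP. If window 1 is included, as the timeline implies, that term is 5/6 of the mean effect over windows 2–6, so it falls short of the peak effect by at least 1/6, and it is not adjusted for baseline. With an immediate, sustained 0.5 SD effect and ρ = .6, its power is about 64%, against 72% for the omnibus interaction and 98% for the baseline-adjusted mean.

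These percentages rest on an assumed effect size, correlation, compound symmetry and 42 analysed patients per arm; the article supplies none of the first three for HRV/BVP. The 5/6 factor needs none of these assumptions, only the inclusion of window 1. The planned group × time and trend × group tests are not affected by the dilution. Because HRV/BVP is secondary, the primary VAS analysis and N = 84 are untouched. The change is worth making, but it does not put the trial's main conclusion at risk.

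**What to change.** In Statistical analyses, for each HRV/BVP parameter:

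- Replace the six-window group main effect with a baseline-adjusted group contrast on windows 2–6, with window 1 as covariate, for example in a mixed model with group, window and group × window. State how the two sessions enter; the session 1 pre-treatment window is the only one recorded before any treatment.
- Keep group × time and trend × group as inferential tests.
- Name in advance the one contrast that decides superiority: the adjusted mean of windows 2–6, group × time, or trend × group, according to the time course expected.
- State that a group main effect over all six windows, if shown at all, is not read as the treatment effect.

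The cost is plan wording and model syntax. No further data, patients or measurements are needed.

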## Discussion

This paper presents the study protocol of a randomized controlled trial on the psychological and physiological effects of a music therapy relaxation intervention for terminally ill patients in palliative care.

One crucial aspect of clinical trials in palliative care research is the design of an adequate control group condition. Different authors took controversial stands regarding the ethical justifiability of applying rigorous, quantitative research methodology in general, and random assignment to study arms in particular to populations of terminally ill patients [31–33]. Withholding potentially effective treatments due to randomization can be particularly problematic. Therefore, we decided to include an active control treatment instead of a no treatment or treatment as usual condition. The experimental and control group intervention share one possible factor of therapeutic change, namely the concept of mindfulness, which is present in both interventions. Hence, if significant between-group differences are to appear, they need to be attributed to factors unique to the music therapy treatment. These are associated with social aspects or the therapeutic relationship on the one hand and characteristics of the live-played music itself, both inherent parts of the definition of music therapy as a health-care profession [5]. Hence, we believe this study design to be appropriate to evaluate the effectiveness of the music therapy relaxation intervention described above. In the course of the analysis and discussion of the study results, we will have to address the question of how the comparison of two active treatments affects the interpretation of our findings. We discuss methodological challenges associated with the implementation of clinical controlled trials on the effectiveness of music therapy in palliative care in more detail in a recently published article [34].

As the study is not supported by external sponsors, no resources for additional study personnel are available. Hence, we expect a long data collection period. As with all interventional studies in palliative care, high drop-out rates are likely to become a particular issue that must be handled in the course of sensitivity analysis.

The research methodology of this study contains some trade-offs and subjective decisions that were discussed intensively in our team (e.g. the decision for a less precise but also less invasive method of HRV measurement). We are confident to have set up a both ethically justifiable and feasible research design that provides high methodological rigor capable of producing valid and reproducible results. To our present knowledge, this study will be the first European RCT on the effects of music therapy in palliative care.

